## 15 DEFINING THE END OF TRIAL

For this study the end of the trial is defined as the last visit of the last patient enrolled in the trial i.e. approximately 6 weeks post completion of BKM120 plus radiotherapy.

The sponsor and the Chief Investigator reserve the right to terminate the study earlier at any time. In terminating the study, they must ensure that adequate consideration is given to the protection of the participants' best interests.

## 16 STATISTICAL CONSIDERATIONS

### 16.1 Sample size determination

If a MTD is reached, it is anticipated that between 6 and 18 evaluable patients will be required for the dose escalation phase of the study. Once the MTD has been reached an expanded cohort of 6 additional patients will be treated at the MTD of BKM120 with palliative RT. Furthermore, an optional cohort of 6 patients will receive 3 weeks of BKM120 prior to RT, bringing the total patient number for the study from 18 to 30.

#### Dose escalation phase

Between 2 and 18 evaluable patients will be recruited to the dose escalation phase. The aim of this Phase I study is to define the MTD of BKM120 when used in combination with palliative thoracic radiotherapy. The starting dose will be 50mg od. Unless DLT occurs this will be escalated to 80mg od and then 100mg od. There will be no further dose escalation beyond 100mg od. The study uses a standard 3+3 cohort design. Three patients will be entered at each dose level. At minimum, the criteria for dose escalation will be that if, by 6 weeks after the 3rd patient in each cohort has completed treatment there is no DLT, then the study will proceed to the next dose level. There will be a continuous evaluation of safety data, and dose escalation will be reviewed in response to any emerging safety information, with the Chief Investigator reserving the right to prolong the duration between cohorts as appropriate. The first cohort of patients will be given the starting dose of 50mg od, consideration will be given to stopping the recruitment early whether 2 or 3 DLTs are observed – consequently the minimum number of patients recruited is 2. If no DLT is observed, 3 patients will be entered at the next higher dose level. If 1 DLT is observed, an additional 3 patients will be entered at the same dose level. This process will be repeated until MTD is reached. This is the dose level at which no more than 1 of 6 evaluable patients or 0 of 3 evaluable patients experience a DLT. As a result, the maximum number of evaluable patients that could be recruited is 18 (6 evaluable patients by 3 dose levels)

#### Dose expansion cohort

To investigate the effect of BKM120 on tumour hypoxia and perfusion, an additional expansion cohort of a further six patients will be treated with BKM120 in combination with radiotherapy at whichever cohort (1-3) corresponds to the MTD.

#### Dose cohort 4

Six patients will be recruited to cohort 4 and will receive 3 weeks of BKM120 at MTD dose prior to RT if cohorts 1-3 have been unable to demonstrate that BKM120 causes changes in tumour hypoxia and perfusion as described in Section 12.1.

The study is planned to include a total of 2-30 patients. All patients will be scheduled to receive the same prescribed dose of radiotherapy.

### 16.2 Definition of primary and secondary endpoints

#### Dose escalation phase

The maximum tolerated dose (MTD) is defined as the highest dose of BKM120 in combination with radiotherapy at which no more than 1 of 6 evaluable patients or 0 of 3 evaluable patients experiences a DLT.

#### Expansion cohort and cohort 4

Changes in F-Misonidazole retention and in blood flow between pre and post BKM120 treatment are defined as response to BKM120 treatment based upon changes in tumour hypoxia and perfusion as detected by F-Miso PET-CT scans and perfusion CT scans respectively. Each patient will be classified as a 'responder' or 'non-responder' on the basis of their pre- and post- BKM120 imaging. Those patients whose imaging demonstrates the presence of a physiological response on either perfusion CT and/or F-Misonidazole PET-CT will be classified as a responder whilst those that do not show a response on either imaging modality will be classed as a non-responder.

### **16.3 Randomisation**

None planned.

## **17 STATISTICAL ANALYSIS PLAN**

A detailed statistical analysis plan will be available from the time the first patient is recruited and will be finalised before any analysis is undertaken. The analysis plan will be written in accordance with the current OCTRU standard operating procedures and will be finalised and agreed by the trial statistician and the CI.

### **17.1 Inclusion in analysis**

All patients enrolled in the study, will be accounted for and included in the analyses. Patients who have completed 56 days on trial or experience a DLT will be included in the dose escalation analysis. The number of patients who were not evaluable, who died or withdrew before treatment began will be recorded. The distribution of follow-up time will be described and the number of patients lost to follow-up will be given.

Variables will be analysed to determine whether the criteria for the study conduct are met. This will include a description of patients who did not meet all the eligibility criteria, an assessment of protocol violations, study drug accountability and other data that impact on the general conduct of the study.

Baseline characteristics will be summarised for all patients who commence BKM120. Patients who do not commence BKM120 or do not complete the required safety observations will be described separately.

Patients will be evaluable for safety and tolerability analysis from the time of their first treatment with BKM120 using NCIC CTCAE v 4.0 scoring and MedDRA coding. Treatment related toxicity will be tabulated by type and grade of toxicity.

Adverse events will be summarised by the number of patients experiencing each type of event. The grades and causality will be reported.

The functional imaging investigations will be used to assess whether BKM120 induces changes in tumour hypoxia and perfusion and to determine whether to open cohort 4. The criteria on which this decision will be based is summarised in Section 12.1.

### **17.2 Subgroup analysis**

Nil planned.

### **17.3 Interim Analyses**

Interim analyses will only be performed if requested by the Independent Early Phase Trial Oversight Committee (IEPTOC).

### **17.4 Procedures for reporting any deviation(s) from the original statistical plan**

Any deviations from the original statistical plan will be described and justified in the final report.

## 17.5 Analysis of safety

### Dose escalation phase

The variables that define the DLTs and safety variables will be summarized by descriptive statistics with patients grouped according to dose level received. Number (with percentages) of patient with and without DLT will also be presented according to dose level.

### Expansion cohort and cohort 4

Safety and toxicity variables will be summarized by descriptive statistics to investigate the safety and feasibility of expanded cohort patients at MTD dose and cohort 4 patients at MTD dose for 3 weeks of BKM120.

## 17.6 Final analysis

The duration of the trial will depend upon whether 3 or 6 evaluable patients are required to complete each of cohorts 1 to 3, and whether there is a requirement to open cohort 4. Final analysis will be performed at least six weeks after the last patient in the trial has completed radiotherapy treatment. However, the analysis of escalation phase will be done and could be showed before expansion phase and/or cohort 4 analyses.

### Expansion cohort and cohort 4

The variables related to the secondary endpoints of changes in  $^{18}\text{F}$ -Misonidazole PET-CT and in blood flow will be summarized by descriptive statistics with patients grouped according to MTD cohort, expansion cohort and cohort 4. Number (with percentages) of patients 'responder' and 'non-responder' will also be presented according to the cohort of the patient.

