### 12.1 Tumour assessment

Response to BKM120 treatment will be based upon changes in tumour hypoxia and perfusion as detected by  $^{18}\text{F}$ -Miso PET-CT scans and perfusion CT scans respectively. These imaging investigations will be performed the day prior to commencing BKM120 treatment, and on the day that radiotherapy treatment commences. The imaging investigations will be repeated prior to the patient receiving their first fraction of radiotherapy.

The rationale for this timing is to observe whether BKM120 can reduce tumour hypoxia and increase tumour perfusion, since both of these changes would be likely to increase the efficacy of radiotherapy treatment.

Establishing the appropriate method for analysis of both imaging techniques is part of the research question. Once established the same method of assessment and the same technique will be used throughout the trial. Changes in tumour-to-blood ratio (TBR) mean and volume will be identified with  $^{18}\text{F}$ -Miso PET-CT imaging and changes in tumour blood flow, blood volume, and mean transit time assessed with perfusion CT imaging.

If there is no change in tumour hypoxia or perfusion following one week of BKM120 treatment, patients will be recruited to cohort 4 where they will receive three weeks of BKM120 at the MTD prior to commencing radiotherapy.

Perfusion CT and dynamic  $^{18}\text{F}$ -Misonidazole PET-CT scans will be performed as summarised in Sections 5.3 and 5.4. Each patient will be classified as a 'responder' or 'non-responder' on the basis of their pre- and post- BKM120 imaging. Those patients whose imaging demonstrates the presence of a physiological response on either perfusion CT and/or  $^{18}\text{F}$ -Misonidazole PET-CT will be classified as a responder whilst those that do not show a response on either imaging modality will be classed as a non-responder.

Patients will only be recruited to cohort 4 if more than 50% of the patients treated with the MTD of BKM120 ( $n = 9$  to 12 evaluable) are defined as non-responders. The following is considered guidance and the statistical analysis of the imaging endpoints will be detailed in the SAP with approval from the DSMC/TSC.

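### Section 17.6 summarises imaging separately for two cohorts on the same regimen and plans no pooled summary of the 9 to 12 patients on whom section 12.1 decides

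*Protocol*

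**What the plan says.** - **Decision group.** Section 12.1: "Patients will only be recruited to cohort 4 if more than 50% of the patients treated with the MTD of BKM120" are non-responders. The section gives the size of this group as 9 to 12 evaluable patients.
- **Reporting groups.** Section 17.6, under its expansion cohort and cohort 4 heading, says the imaging variables will be "summarized by descriptive statistics with patients grouped according to MTD cohort, expansion cohort and cohort 4". Numbers and percentages of "patients 'responder' and 'non-responder' will also be presented according to the cohort of the patient". No combined MTD group is listed.
- **Purpose of the expansion.** Section 16.1: "To investigate the effect of BKM120 on tumour hypoxia and perfusion, an additional expansion cohort of a further six patients will be treated" at the MTD.
- **Definitions.** Section 6.1 says who is evaluable for the imaging endpoints, and section 16.2 defines imaging response. Both do so only under a heading for the expansion cohort and cohort 4. The dose-escalation parts of those sections deal with DLT only.
- **Regimen.** By the section 8.1 table and the schedule of events, the escalation cohort at the MTD and the expansion cohort receive the same BKM120 dose on days 1 to 14 and 20 Gy in 5 fractions on days 8 to 14, with scans on day -1 and day 8. Cohort 4 has a 28-day schedule.
- **Deferral.** Section 12.1 calls its imaging criteria guidance and leaves the statistical analysis of imaging to the SAP.

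**The concern.** Whether BKM120 alters tumour hypoxia and perfusion is the only secondary objective in section 3. Section 12.1 treats everyone on the 14-day MTD regimen as one group when it acts on the imaging. Section 17.6 then divides that group when it reports the imaging.

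Two things are at stake. The first is precision: the change in TBR mean and volume, BF and MTT would be described in 3 or 6 patients and again in 6, not once in 9 to 12. The second is clarity: rows this small can disagree with each other, or with the pooled percentage that settled cohort 4, by chance alone, and the protocol does not say which row is the main result.

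The definitions add to this. Sections 12.1 and 17.6 both use imaging from the escalation cohort at the MTD, but 6.1 does not say when such a patient counts as evaluable for imaging.

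**Working it through.** **1. The plan's own figure.** By the MTD definition (0 of 3 or no more than 1 of 6 with DLT), the escalation cohort at the MTD has 3 or 6 evaluable patients. The expansion cohort has 6. So 3 + 6 = 9 and 6 + 6 = 12, which is the range in 12.1. The decision group is therefore the two cohorts together. The lower figure assumes that all three escalation patients have both scans; 6.1 provides for replacement of patients without scans only in the expansion cohort and cohort 4.

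**2. Precision of the mean change.** The half-width of a 95% t-interval is t(0.975, n-1) × SD / √n. The multiplier of the SD is:

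| Group | n | t | t/√n |
|---|---|---|---|
| MTD cohort, smaller case | 3 | 4.303 | 2.484 |
| MTD cohort, larger case, or expansion | 6 | 2.571 | 1.049 |
| Pooled | 9 | 2.306 | 0.769 |
| Pooled | 12 | 2.201 | 0.635 |

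Relative to the expansion cohort alone, pooling narrows the interval by 1 - 0.769/1.049 = 27% (n = 9) or 1 - 0.635/1.049 = 40% (n = 12). This needs no value for the SD, only that it is the same in both cohorts.

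The absolute size does need an SD, and the protocol gives none for its own endpoints. The 14% in 12.1 is a tumour-to-muscle figure from head and neck cancer. Taking it as the SD of the percentage change is an assumption, so half and double that value are shown too:

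| SD (points) | n = 3 | n = 6 | n = 9 | n = 12 |
|---|---|---|---|---|
| 7 | 17.4 | 7.3 | 5.4 | 4.4 |
| 14 | 34.8 | 14.7 | 10.8 | 8.9 |
| 28 | 69.6 | 29.4 | 21.5 | 17.8 |

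**3. Precision of the responder percentage.** The exact (Clopper-Pearson) 95% interval at an observed 50% is 12% to 88% for 3/6 and 21% to 79% for 6/12.

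**4. How often the rows disagree.** Let a be the number of non-responders among m = 3 or 6 MTD-cohort patients and b the number among 6 expansion patients. Take a and b as independent binomials with the same true rate p, and sum P(a)P(b) over the discordant pairs. The rule is met when non-responders exceed 50%, so an exact 50% does not meet it.

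| m | True non-responder rate | Rows strictly opposite sides of 50% | Rows differ under the rule | Expansion strictly opposite pooled | Expansion differs from pooled under the rule |
|---|---|---|---|---|---|
| 3 | 0.4 | 0.308 | 0.405 | 0.050 | 0.147 |
| 3 | 0.5 | 0.344 | 0.500 | 0.059 | 0.215 |
| 3 | 0.6 | 0.308 | 0.487 | 0.050 | 0.229 |
| 6 | 0.4 | 0.195 | 0.294 | 0.048 | 0.147 |
| 6 | 0.5 | 0.236 | 0.451 | 0.054 | 0.226 |
| 6 | 0.6 | 0.195 | 0.496 | 0.048 | 0.248 |

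Hand check of one cell (m = 3, p = 0.5, expansion strictly opposite pooled): the pairs are a = 0, b = 4 (67% against 4/9 = 44%) and a = 3, b = 2 (33% against 5/9 = 56%). Each has probability 1/8 × 15/64 = 0.0293, and together they give 0.059.

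**The case against.** **Deferral to the SAP.** Section 12.1 sends the imaging analysis to the SAP, and a total column or confidence interval is ordinary SAP content. That would answer a complaint about missing detail. It answers this one only in part, because 17.6 does not leave the grouping open: it states one, and that one omits the group used in 12.1.

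**Pooling is not excluded.** A reader might infer that the pooled result is never produced. The documents do not support that. The 12.1 rule requires the pooled responder percentage, 17.1 refers to that rule, and nothing in 17.6 forbids a total. A reader could add the two responder counts. A pooled mean could be rebuilt if numbers and means are printed for each cohort, but a pooled median could not, and 17.6 does not say which statistics will be given.

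**Section 16.1.** A reader might also infer that 16.1 gives the imaging question to the six expansion patients alone, a third and conflicting analysis group. That over-reads it. The sentence explains why six further patients are recruited, and they add to those already treated at the MTD, which is how 12.1 reaches 9 to 12.

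**Reasons to show the cohorts apart.** There are some. Section 6.1 replaces patients without scans only in the later cohorts. Section 8.3 says the liver guidance was updated after escalation was complete. Appendix 7 lists a change to ECOG eligibility, numbered after the amendment on liver and mood guidance. These justify keeping the separate rows. They do not justify leaving out the pooled one.

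**Size.** The higher disagreement figures count an exact 3/6 as being on the other side of the line, and 17.6 attaches no decision to any row. The strict figures are the fairer description of conflicting rows. The plan is descriptive and proposes no confidence interval, so the half-widths measure the information available, not a planned output.

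**Definitions.** Section 12.1 describes the responder classification for each patient without limiting it to a cohort, so the gap in 16.2 is one of heading. The gap in 6.1 is one of substance.

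**Conclusion.** The point holds as a minor one. The final imaging analysis names two cohorts on one regimen as separate groups. It plans no pooled summary of the continuous changes and no pooled row, although the protocol's one imaging decision rests on the pooled group.

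The cost in precision is an interval for the mean change that pooling would narrow by about 27% to 40% relative to the expansion cohort alone, assuming a common SD. At true responder rates of 40% to 60%, the same in both cohorts and with independent patients, the separate rows fall strictly on opposite sides of 50% in about 20% to 34% of trials, or 29% to 50% if an exact 50% counts as not exceeding it. The expansion row lies strictly opposite the pooled percentage in about 5% to 6%, and gives a different answer under the 12.1 rule in 15% to 25%.

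No test, error rate or power is affected, and the cohort 4 decision in 12.1 already uses the pooled group. The effect is on how precisely and clearly a secondary, descriptive endpoint is reported.

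**What to change.** - In 17.6, name all imaging-evaluable patients treated at the MTD on the 14-day schedule (MTD escalation cohort plus expansion cohort) as the main imaging summary. Report the change in each parameter and the responder percentage with 95% confidence intervals, exact for the percentage.
- Keep the separate MTD-cohort and expansion-cohort rows as supportive. Keep cohort 4 separate, because its schedule differs.
- Extend the imaging evaluability definition in 6.1 and the response definition in 16.2 to the MTD escalation cohort, and carry the same group into the SAP.

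The cost is a sentence in 17.6, small wording changes in 6.1 and 16.2, and one more table column. No new patients, scans or data are needed. The downside is that the pooled row mixes two recruitment phases with some differences in guidance and eligibility, which the retained rows would show.

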## 18 TRIAL COMMITTEES

### 18.1 Trial Management Group (TMG)

The Chief Investigator will chair a TMG with responsibility for overseeing the successful conduct and publication of the trial in accordance with the protocol. The TMG will review safety and dose escalations with advice from the Independent Early Phase Trial Oversight Committee (see section 18.2 below). It will provide regular progress reports as required by the applicable steering committees and governance bodies. Members of the TMG are:

- Chief Investigator
- Clinical Trial Coordinator
- Trial management / QA
- Trial Statistician
- External Member

### 18.2 Data and Safety Monitoring

There is no Data and Safety Monitoring Committee. The IEPTOC will be in place to monitor the safety and progress of the trial.

### 18.3 Trial Steering Committee

The role of the Trial Steering Committee will be fulfilled by the IEPTOC.

## 19 DATA MANAGEMENT

### 19.1 Database considerations

Data management will be performed via a web-based, bespoke trial database (OpenClinica). OpenClinica is a dedicated and validated clinical trials database designed for electronic data capture. See: <http://www.openclinica.org>.

The Chief Investigator will act as Data Custodian for the trial.

## 19.2 Electronic case reports forms (eCRFs)

The Investigator and study site staff will ensure that data collected on each subject is recorded in the CRF as accurately and completely as possible. The CRFs will not contain any source data. All appropriate laboratory data, summary reports and Investigator observations will be transcribed into the CRFs from the relevant medical record(s). Please ensure that

- the relevant CRFs are completed and signed off by the Investigator for each study patient
- all CRF data are verifiable in the source documentation or the discrepancies must be explained.
- CRF sections are completed in a timely fashion, as close to the visit or event being recorded as possible.
- Data queries are resolved and documented by authorised study staff, giving a reason for the change or correction where appropriate.

The above considerations also apply to patients who are withdrawn early. If a patient withdraws from the study, the reason must be noted on the appropriate form and the patient must be followed-up as per protocol.

## 19.3 Accounting for missing, unused, or spurious data.

Missing data will be chased up and supplemented where possible after consultation with the investigator. The control of the correctness of the data is performed with ranking tests, validity tests and consistency checks. Unused data will be retained as for used data.

# 20 CLINICAL STUDY REPORT

All clinical data will be presented at the end of the study as data listings. These will be checked to confirm the lists accurately represents the data collected during the course of the study. The trial data will then be locked and a final data listing produced. The clinical study report will be based on the final data listings. The locked trial data may then be used for analysis and publication.

# 21 STUDY SITE MANAGEMENT

## 21.1 Study site responsibilities

The Principal Investigator (the PI or lead clinician for the study site) has overall responsibility for conduct of the study, but may delegate responsibility where appropriate to suitably experienced and trained members of the study site team. All members of the study site team must complete the delegation log provided prior to undertaking any study duties. The PI must counter sign and date each entry in a timely manner. Study team members must provide a current CV giving evidence of valid and up to date GCP training for inclusion in the study file. Copies of the delegation log and CVs will be provided to the trial office on request. Sites must report any unintended deviations/violations to OCTO according to the procedure outlined during site initiation training.

For further information on trial responsibilities, please refer to the ICH GCP guideline (E6). Copies can be obtained from [www.ich.org](http://www.ich.org)

## 21.2 Study site set up and activation

A Principal Investigator should lead the study at the site, providing the local study office with all core documentation and attend 'Site Training Call' organised by the trial office before the site becomes activated (usually carried out as a telephone conference call or personal visit). The trial office will call to check that the site has all the required study information/documentation and is ready to recruit. The site will then be notified once they are activated on the BKM120 database and able to register.

